### GSD-Young

Self-management is an active and proactive process that involves activities and goals and that is continuously ongoing. It involves shared but shifting responsibility for diabetes care and decision making between the child and their parents, and it is a process that also involves health care staff. It is important to be aware that self-management may differ from one parent/child dyad to another [28]. Person-centred care highlights the importance of knowing the person behind the patient to engage the person as an active partner in his/her own care and treatment [29]. Guided self-determination (GSD) is an empowerment-based, person-centred, reflection and problem solving method intended to guide the patient to becoming self-determined and developing life skills to manage difficulties in diabetes self-management using worksheets. GSD helps the patient and the health care staff to overcome barriers to empowerment. It has been effective both in individual and group training of adults with type 1 diabetes [30]. [name] et al. have adapted GSD for adolescents and their parents as Guided self-determination-Young (GSD-Y) and there is an ongoing study of adolescents with type 1 diabetes in Denmark [31]. This study will evaluate the effect of an intervention using GSD-Y in groups of adolescents and their parents. It will be carried out at routine outpatient clinics.

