### Randomization

Adolescents and their parents who are willing to participate in the study will be divided consecutively into groups depending on which pump model they have chosen. The groups will then be randomized to either intervention or control. The main reason for group randomization is to make the study feasible within a reasonable time. It is not possible to provide enough staff to start different pump models at the same time. Our experience indicates that there are no differences in distribution between the sexes among those starting CSII; therefore, we have not stratified for gender.

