### Intervention

All adolescents and their parents (both the control group and the intervention group) will receive insulin pump standard start training, including technical skills and how to use carbohydrate counting with CSII. The parents will simulate diabetes by wearing a pump containing saline and test their blood glucose before the child starts insulin pump treatment. The education intervention will be conducted in connection with starting CSII (on three occasions) and on four occasions in the first 4 months after starting CSII. Each session will last 1.5-2 hours. The intervention will be performed by two diabetes nurses (Figure 1). The GSD-Y method will be used with structured reflection sheets. The first reflection sheet will be sent to participants before their first appointment. For subsequent appointments, the reflection sheet for the next meeting will be distributed at that appointment and completed before the next appointment. By filling in the reflection sheet using their own words and drawings, adolescents and their parents systematically explore and express their own experiences and difficulties with diabetes in daily life (Table 1). In the dialogue, different communication models are used, including mirroring, active listening and value-clarifying responses [30,31]. Three diabetes nurses and two dieticians have been trained to use GSD. Together with the creators of GSD and GSD-Y ([name] and [name]) [30,31], we have adjusted GSD-Y so that it fits this study. The worksheets have been translated into Swedish and retranslated by a Danish and Swedish speaking person.

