### Statistical analysis and power calculation

To detect a difference of 6 mmol/mol in HbA1c (SD: ± 9.1), at least 37 participants are required in each group (power 80% and alpha 0.05). SD is calculated from the available participants in the actual clinics (n = 160) at study start, mean HbA1c: 74.2 ± 9.1 mmol/mol. Allowing for patient withdrawals and those lost to follow up, 80 patients will be included in the study. All analysis will be conducted on an intention-to-treat basis. The differences between the groups will be analysed using an un-paired t-test with a 95% confidence interval and p < 0.05 considered as significant. A repeated measures ANOVA will be used for before and after comparisons in the groups, using the same confidence interval and level of significance. When testing differences between groups using Disabkids, ‘Check your health’, DFCS and Swe-DES 23, the same statistical analysis will be used.

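### Pump-start groups are randomised, but the between-arm t-test and the sample size treat adolescents as independent, so precision is overstated if outcomes correlate within groups

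*Protocol article*

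**What the plan says.** Under Randomization, consenting families "will be divided consecutively into groups depending on which pump model they have chosen", and then: "The groups will then be randomized to either intervention or control". The article calls this group randomisation and gives its reason: "The main reason for group randomization is to make the study feasible within a reasonable time". The GSD-Young section says the intervention is used in groups of adolescents and parents. Table 1 lists seven visits, three around pump start and four afterwards.

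Under Statistical analysis and power calculation, the between-arm rule is: "The differences between the groups will be analysed using an un-paired t-test with a 95% confidence interval". A repeated measures ANOVA is named for before-and-after comparisons. For Disabkids, 'Check your health', DFCS and Swe-DES 23, "the same statistical analysis will be used". The sample size is at least 37 per arm for a 6 mmol/mol difference in HbA1c with SD 9.1, 80% power and alpha 0.05, raised to 80 in total to allow for losses.

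The article does not mention clustering, an ICC, a design effect or a term for the randomised group.

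**The concern.** The unit of randomisation is the pump-start group, while the unit of the named test is the adolescent. An un-paired t-test estimates the standard error of the arm difference from the spread between individuals, as if each had been allocated separately. If members of a group resemble each other, the variance between groups also enters the arm difference, and the t-test leaves it out.

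Some positive correlation is plausible. Members share a pump model and a recruitment period and, in the intervention arm, sessions on shared responsibility and problem solving. Several questionnaires measure things that group discussion could move directly, such as family conflict and empowerment. Because pump model defines the groups, any effect of model on HbA1c is also between-group variance.

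At stake are the error rate and interval coverage of the primary comparison and of every questionnaire comparison. With a positive ICC, the error favours declaring a difference.

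**Working it through.** **1. The plan's own figure.** Inputs from Statistical analysis and power calculation: difference 6, SD 9.1, alpha 0.05, power 80%. Two-sided formula for independent patients:

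n per arm = 2 × (1.960 + 0.842)² × 9.1² / 6² = 36.1, rounded up to 37.

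This matches the stated 37 (a t-based solution gives 37.09; a one-sided formula would give 29). The match needs a design effect of 1, so the sample size makes the same independence assumption as the test.

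**2. Assumptions.** Group size m and ICC are not in the article. I take m = 4 to 8 (20 to 10 groups for 80 adolescents) and ICC 0.01, 0.05 and 0.10, the same in both arms.

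**3. Formulas.**
- Design effect: DE = 1 + (m − 1) × ICC.
- True type I error of the naive test: 2 × [1 − Φ(1.96/√DE)].
- Correct SE divided by naive SE: √DE.
- Shortfall in naive interval width: 1 − 1/√DE.

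**4. Results.** The simulation column is the planned t-test under no effect, 40 per arm, 20,000 runs per setting.

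| m | ICC | DE | Type I error, formula | Type I error, simulated | √DE |
|---|---|---|---|---|---|
| 4 | 0.01 | 1.03 | 5.3% | 5.5% | 1.015 |
| 4 | 0.05 | 1.15 | 6.8% | 6.9% | 1.072 |
| 4 | 0.10 | 1.30 | 8.6% | 8.6% | 1.140 |
| 5 | 0.05 | 1.20 | 7.4% | 7.1% | 1.095 |
| 5 | 0.10 | 1.40 | 9.8% | 10.0% | 1.183 |
| 8 | 0.01 | 1.07 | 5.8% | 5.6% | 1.034 |
| 8 | 0.05 | 1.35 | 9.2% | 9.2% | 1.162 |
| 8 | 0.10 | 1.70 | 13.3% | 13.1% | 1.304 |

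At ICC 0 the simulated error is 4.9-5.2%, as it should be. A t-test on group means held 4.7-5.3% in simulations of 20 groups of 4, 16 of 5 and 10 of 8.

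**5. Interval width.** Over DE 1.15 to 1.70 the correct SE is 7% to 30% larger than the naive SE. The naive interval is therefore too narrow by 1 − 1/1.072 = 7% to 1 − 1/1.304 = 23%. This counts the SE only; the smaller degrees of freedom of a group-level test widen the correct interval further.

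**6. Power of a group-level test, all 80 analysed in equal groups.** SE = 9.1 × √(2 × DE/40), noncentrality = 6/SE, degrees of freedom = number of groups − 2.
- m = 4, ICC 0.05: SE 2.18, noncentrality 2.75, 18 df, power about 74%.
- m = 8, ICC 0.05: SE 2.36, noncentrality 2.54, 8 df, power about 61%.
- m = 8, ICC 0.10: SE 2.65, noncentrality 2.26, 8 df, power about 51%.

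**The case against.** The strongest reply is that the size of the problem is unknown. Without an ICC or a group size, nothing in the article shows that the error rate is materially wrong. At ICC 0.01 with groups of 4 to 8 it is 5.3-5.8%, which is slight. This stands as a limit on size and makes the direction conditional on a positive ICC. It does not rescue the test, because the article fixes a method that is valid only if the ICC is zero and gives no ground for that.

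Three stronger readings are tempting, and the article does not support them.

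- **That every planned test is inflated by these amounts.** The repeated measures ANOVA is named for before-and-after comparisons within arms. Clustering acts there only through correlation of change scores within groups, and none of the figures above describe it.
- **That shared trainers and group teaching of controls are facts of the design.** The Intervention section says "The intervention will be performed by two diabetes nurses". If the same two serve every group, they add no between-group variance within that arm; three nurses are trained, so rotation is possible but not stated. Group teaching of controls is an inference from the staffing remark under Randomization. If clustering mattered only in the intervention arm, the inflation would be about (DE + 1)/2: DE 1.15 becomes 1.075 (type I error about 5.9%) and DE 1.70 becomes 1.35 (about 9.2%).
- **That the interval is up to 30% too narrow.** Thirty per cent is how much larger the correct SE is; the shortfall in width is 23%.

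It might also be said that an unseen analysis plan could correct this. The article does not leave the test open, however; it names one that conflicts with its own randomisation.

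**Conclusion.** The concern holds for the between-arm comparison of HbA1c and of each questionnaire, and for the sample size. Whole groups are randomised, and the named test ignores them. The mismatch is certain from the text. The direction, p-values too small and intervals too narrow, holds for any positive ICC.

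The size rests on assumed groups of 4 to 8 and a common ICC in both arms. On that basis the true type I error runs from just above 5% at ICC 0.01 to about 13% at ICC 0.10 with groups of 8. The article does not allow a choice of one value within that range. The plan should be changed even so, because the remedy is cheap and the test is otherwise valid only under an independence assumption that the design does not provide.

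**What to change.** Record a pump-start group identifier for every participant now; without it, later correction may be impossible. Replace the un-paired t-test with one prespecified between-arm analysis: a linear mixed model with random intercepts for randomised group and for participant across visits, with Kenward-Roger degrees of freedom. Name a t-test on group means as the sensitivity check. Apply this to HbA1c and to each questionnaire, and report the ICC with the number and size of groups.

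The cost is a change of analysis wording, one extra data field and wider intervals. The 80% power claim must also be restated with an assumed group size and ICC. With 80 analysed in equal groups of 4 to 8, power for 6 mmol/mol is roughly 74% to 61% at ICC 0.05, and about 51% for groups of 8 at ICC 0.10. No extra patients are proposed. For scale, multiplying 37 by the design effect gives 43 to 50 per arm at ICC 0.05 and 49 to 63 at ICC 0.10, before any allowance for the small number of groups or for losses.

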
**Table 2 T2:** Data collection

**Before starting CSII**	• HbA1c, height, weight, insulin requirement, mean frequency of self-monitoring of blood glucose (SMBG)
	• ‘Check your health’, Disabkids, DFCS, Swe-DES 23 and treatment satisfaction.
**6 and 12 months after starting CSII**	• Same measures as before starting CSII
	• Frequency of bolus doses and usage of carbohydrate counting

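### The between-arm t-test names no baseline covariate although every needed baseline is collected; adjusting for baseline would gain precision and remove conditional bias at no data cost

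*Protocol article*

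**What the plan says.** The Statistical analysis and power calculation section gives one method for comparing the arms: "The differences between the groups will be analysed using an un-paired t-test", with a 95% confidence interval and a 5% significance level. No covariate is named. The only method there that clearly uses the baseline measurement is assigned elsewhere: "A repeated measures ANOVA will be used for before and after comparisons in the groups". The questionnaires follow the same route: "When testing differences between groups using Disabkids, ‘Check your health’, DFCS and Swe-DES 23, the same statistical analysis will be used".

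Table 2 (Measures and data collection) shows that the baselines exist. Its row for the time before pump start opens with "HbA1c, height, weight, insulin requirement, mean frequency of self-monitoring of blood glucose (SMBG") and goes on to list 'Check your health', Disabkids, DFCS, Swe-DES 23 and treatment satisfaction. The same measures are repeated at 6 and 12 months.

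The Randomization section says that participants are formed into groups by chosen pump model and that these groups are randomised. It gives neither the number nor the size of the groups, and it describes no balancing on HbA1c.

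The sample size is stated as follows: "To detect a difference of 6 mmol/mol in HbA1c (SD: ± 9.1), at least 37 participants are required in each group", with "power 80% and alpha 0.05".

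**The concern.** The trial measures each patient's HbA1c and questionnaire scores before treatment, then compares the arms with a test that takes no covariate. Two things are at stake.

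- **Precision.** To the extent that baseline predicts follow-up, an unadjusted comparison of follow-up values leaves explainable variation in the error term.
- **Conditional bias.** If the arms happen to differ at baseline, a comparison of follow-up values carries part of that difference into the estimated effect. Such a difference is likelier here than under individual randomisation if patients within a group are correlated, because whole groups are allocated and there are fewer randomised units than 80 patients.

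The text also leaves open which variable is tested. If it is the change from baseline, the imbalance is subtracted and the concern becomes mainly one of efficiency.

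**Working it through.** **Inputs from the protocol article.** Difference 6 mmol/mol, SD 9.1 mmol/mol, 80% power, alpha 0.05, 37 per group, 80 patients in total (40 per arm if allocation is equal). The SD is cross-sectional: "SD is calculated from the available participants in the actual clinics (n = 160) at study start".

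**Assumed, because the article does not give them.** The baseline-to-follow-up correlation r (0.3 to 0.7), equal SDs at baseline and follow-up, and, for one illustration only, group size and intracluster correlation (ICC).

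**1. The plan's own figure.** n per arm = 2 × [9.1 × (1.960 + 0.842) / 6]² = 36.1, rounded up to 37. This is the two-sided, unadjusted two-sample calculation, and it reproduces. Exact-t power at 37 per arm is 79.9%.

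**2. Power by choice of analysis** (two-sided exact t, 37 per arm, patients taken as independent). ANCOVA residual SD = 9.1 × √(1 − r²). Change-score SD = 9.1 × √(2(1 − r)).

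| Assumed r | ANCOVA SD | ANCOVA power | Change SD | Change-score power | Follow-up t-test power |
|---|---|---|---|---|---|
| 0.3 | 8.68 | 83.5% | 10.77 | 65.7% | 79.9% |
| 0.5 | 7.88 | 89.8% | 9.10 | 79.9% | 79.9% |
| 0.7 | 6.50 | 97.5% | 7.05 | 95.1% | 79.9% |

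The follow-up t-test carries 1/(1 − r²) times the ANCOVA variance: 1.10, 1.33 and 1.96. The change-score test carries 2(1 − r)/(1 − r²) = 2/(1 + r) times that variance: 1.54, 1.33 and 1.18. With equal variances, change scores are less efficient than follow-up values when 2(1 − r) > 1, that is, when r < 0.5. With unequal variances the threshold becomes r < SD(baseline) / (2 × SD(follow-up)).

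**3. Size of a chance baseline difference.** With 40 independent patients per arm, SE = 9.1 × √(2/40) = 2.03 mmol/mol. A baseline gap of 3 mmol/mol or more in either direction then has probability 14%. For illustration, take groups of 8 (10 groups) and an ICC of 0.05 to 0.10. The design effect 1 + 7 × ICC is 1.35 to 1.70, the SE is 2.36 to 2.65, and the probability is 20% to 26%.

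**4. What such a gap does to a follow-up t-test.** The expected shift is r × 3 = 0.9, 1.5 and 2.1 mmol/mol at r = 0.3, 0.5 and 0.7, which is 15%, 25% and 35% of the 6 mmol/mol target. Given a 3 mmol/mol gap and independent patients, the conditional type I error is about 6%, 8% and 10%. Averaged over all randomisations, chance imbalance leaves it at the nominal level.

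**The case against.** The strongest case for the plan is that it is consistent with itself. The 37 per group is the number for an unadjusted comparison, and on the plan's own terms that comparison delivers the stated power. An unadjusted difference is unbiased over randomisation. This stands: the point is about a better use of data already collected, not about an error in the plan's arithmetic.

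Several stronger readings are tempting, and the article does not support them.

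- **Baseline is ignored and imbalance goes uncorrected.** A reader might infer this, but the outcome variable of the t-test is not stated. The Abstract speaks of comparing data at baseline, 6 and 12 months within and between groups, and the Discussion speaks of determining changes. A change-score test is therefore a fair reading, and it would subtract the imbalance.
- **Only a few groups are randomised.** The number is not given. What follows from the text is only that there are fewer units than 80.
- **Change scores always lose to follow-up values below r = 0.5.** That rule needs equal variances. The entry cut-off truncates baseline HbA1c but not follow-up, so the follow-up SD may be larger and the threshold lower.
- **Adjustment recovers the power lost to clustering.** Nothing here shows that. Every power figure above ignores clustering, and any recovery would depend on how much of the between-group variation baseline explains.

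It is also fair that the gain may be modest. Excluding patients with HbA1c below 63 mmol/mol tends to lower r, and at r = 0.3 power rises only from about 80% to 84%.

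Two replies to the point do not hold. The repeated measures ANOVA does not fill the gap, because it is assigned to before-and-after comparisons in the groups. Nor is this a detail left to a fuller document: the test is named. An unseen analysis plan might add adjustment, but the published text does not.

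**Conclusion.** The point holds as a recommendation to improve the analysis; it does not show the t-test to be invalid. The named between-arm test has no baseline covariate, and the baselines for HbA1c and all four instruments are collected. On either reading of the outcome variable, ANCOVA is at least as efficient; on the follow-up reading it also removes bias conditional on an observed imbalance.

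The direction of the gain is secure, but its size is not. It rests on a correlation that the article does not give, on the plan's SD applying at follow-up, and on patients being treated as independent. The lower part of the range is the more cautious expectation.

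**What to change.** - Make the primary between-arm analysis a linear model of follow-up HbA1c on arm, adjusted for baseline HbA1c.
- Analyse each questionnaire in the same way, adjusted for its own baseline score.
- Keep the un-paired t-test as an unadjusted sensitivity analysis, and state whether it is on follow-up values or on changes.
- Fix this wording before outcome data are seen, so that adjustment cannot look like a response to an observed imbalance.

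The cost is a change of analysis wording: no new visit, measurement or patient is needed, and the sample size can stay as it is for this point. Allowing for the randomised start group in the same model is a separate clustering issue, which baseline adjustment alone does not repair.

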**Methods/design:**

This study is designed as a randomized, controlled, prospective, multicentre study. Eighty patients between 12–18 years of age who are planning to start CSII will be included. All adolescents and their parents will receive standard insulin pump training. The education intervention will be conducted when CSII is to be started and at four appointments in the first 4 months after starting CSII. The primary outcome is haemoglobin A1c levels. Secondary outcomes are perceived health and QoL, frequency of blood glucose self-monitoring and bolus doses, and usage of carbohydrate counting. The following instruments will be used: Disabkids, ‘Check your health’, the Diabetes Family Conflict Scale and the Swedish Diabetes Empowerment Scale. Outcomes will be evaluated within and between groups by comparing data at baseline, and at 6 and 12 months after starting treatment.

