### Participants and recruitment

Eighty patients between 12 and 17.99 years who are planning to start CSII will be included. Patients will be excluded if their diabetes has been diagnosed within the past year, HbA1c is < 63 mmol/mol, insulin requirement is < 0.5 IU/kg, if the patient is using continuous glucose monitoring when they start CSII, or if the teenager or their parents have difficulties understanding Swedish. Approximately 4 times per year, information meetings about pump treatment and different insulin pump models will be held at the study sites. Oral and written information about the present study will be given to patients who fulfil the inclusion criteria. Written informed consent for participation in the study will be obtained from the parents and adolescents.

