## Discussion

The aim of our study is to provide an educational program in an urban area, and its success depends on how well the study participants represent the population of interest. Previous studies have indicated that children with many diabetes-related conflicts have poorer glycaemic control, and thus, it is important that this group be represented in the study sample [27]. We have chosen to use HbA1c measured at the visit before the planned start of CSII as the inclusion criterion. An alternative, which is common in studies with adults, is to use a mean result from three HbA1c tests taken in the last year. We did not use this latter method as part of the entry criteria because some of the potential patients will have been diagnosed with diabetes for only a short time, and there is a risk of using an HbA1c result from a remission period. GSD is an empowerment-based program, and we have thus chosen to use Swe-DES 23, which is sensitive to change. Previous studies show that unclear responsibility distribution can explain omitted bolus doses and family conflicts, and we will also use DFCS, which is one of the most widely used measures of diabetes-specific family conflict [21,27]. To detect changes in perceived physical and emotional health, social relationships, general QoL and the burden of diabetes, we will use the measures Disabkids and ‘Check your health’ [33-35]. There is a risk that there will be high scores on perceived QoL already at baseline, but it is important to detect both rates of deterioration and improvement. We also want to observe any changes in the burden of diabetes. We will measure treatment satisfaction with one question; we have used this question in previous studies and it has been shown to be sufficient for measuring treatment satisfaction [18]. The intervention will take 4 months and evaluation with measurements of perceived QoL will be performed at baseline, 6 and 12 months to allow comparisons and to determine any changes. Previous research has shown that there is an initial improvement in the first months after the start of treatment using an insulin pump, which later subsides [14,16]. We believe that starting an insulin pump together with an empowerment-based, person-centred education model leads to retention of improved glycaemic control, QoL, responsibility distribution and reduced diabetes-related conflicts in the family.

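### The within-arm before-after ANOVA is planned as a significance test alongside the between-arm t-test, but a fall in HbA1c within one arm cannot be attributed to GSD-Y

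*Protocol article*

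**What the plan says.** The section on statistical analysis and power calculation names two analyses. The first is between arms: "The differences between the groups will be analysed using an un-paired t-test with a 95% confidence interval and p < 0.05 considered as significant". The second is within arms: "A repeated measures ANOVA will be used for before and after comparisons in the groups, using the same confidence interval and level of significance". Neither is ranked above the other, and the within-arm test is not called descriptive. The abstract confirms both: "Outcomes will be evaluated within and between groups by comparing data at baseline, and at 6 and 12 months after starting treatment". The same section extends this analysis to the questionnaires.

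The sample size rests on the between-arm contrast: "To detect a difference of 6 mmol/mol in HbA1c (SD: ± 9.1), at least 37 participants are required in each group" ("power 80% and alpha 0.05").

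Three other statements bear on what a within-arm change can mean:
- Under Intervention, both arms receive the standard pump-start training; all participants are starting CSII.
- Under Participants and recruitment, patients are excluded if "HbA1c is < 63 mmol/mol". The Discussion adds: "We have chosen to use HbA1c measured at the visit before the planned start of CSII as the inclusion criterion". It considers a mean of three tests and decides against it.
- The Discussion cites earlier research in which control improves in the first months on a pump and the gain then fades.

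**The concern.** A before-after test in one arm asks whether HbA1c changed, not whether GSD-Y changed it. At least two causes unrelated to GSD-Y push HbA1c down in both arms: starting the pump, and regression to the mean after selection on one high reading. Randomisation balances these between arms but does not remove them from the change within an arm.

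Two misreadings become possible at the 0.05 level. A significant fall in the GSD-Y arm may be reported as an effect of the programme. Or a significant fall in that arm and a non-significant one in controls may be taken as a difference between arms, which it does not test. The stated aim of retaining improved control makes this tempting, because retention sounds like a question about the course over time in the GSD-Y arm. The longitudinal analysis, as worded, does not compare that course with the control arm's.

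**Working it through.** **1. The plan's own figure.** Inputs from the power calculation: difference 6, SD 9.1, power 80%, alpha 0.05 (taken as two-sided).

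n per arm = 2 × (1.960 + 0.842)² × 9.1² / 6² = 36.1, rounded up to 37. The stated 37 is reproduced, so the trial is sized for the between-arm comparison.

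**2. How easily a within-arm test becomes significant.** Assumptions not in the documents: a true fall of 3 mmol/mol in both arms, no GSD-Y effect, SD 9.1 at each visit, and within-person correlation r. A two-visit paired t-test with n = 37 approximates the ANOVA.

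SD of change = 9.1 × √(2(1 − r)); noncentrality = 3 / (SD of change / √37). With p the probability that one arm is significant, the misleading pattern (GSD-Y arm significant, control arm not) has probability p(1 − p).

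| r | SD of change | Noncentrality | p | p(1 − p) |
|---|---|---|---|---|
| 0.5 | 9.10 | 2.01 | 50% | 25% |
| 0.7 | 7.05 | 2.59 | 71% | 21% |
| 0.9 | 4.07 | 4.48 | 99% | 1% |

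At r = 0.9 discordance is rare, but both arms show a significant fall almost every time.

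Conversely, one arm of 37 has 80% power for a mean change of 4.3, 3.3 or 1.9 mmol/mol at r = 0.5, 0.7 or 0.9. A shared change well below the design difference of 6 is enough.

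**3. The three-visit ANOVA.** This was simulated with 4,000 trials per scenario, 37 per arm, entry at 63 or more, no GSD-Y effect and individual randomisation. The parent distribution was 74.2 ± 9.1 or an illustrative 70 ± 12, with r = 0.6 or 0.8.

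| Assumed pump effect at 6 / 12 months | GSD-Y arm significant | GSD-Y arm only |
|---|---|---|
| 0 / 0 | 6–25% | 6–19% |
| 3 / 1 | 72–89% | 8–21% |
| 5 / 2 | 97–99.9% | 0–2% |

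The 12-month between-arm t-test was significant in 4.5 to 5.4% of trials throughout.

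**4. Regression to the mean.** Expected fall = (1 − r) × (mean of those selected − mean of the parent population), assuming normality and that the screening value is also the baseline. The source figure is: "SD is calculated from the available participants in the actual clinics (n = 160) at study start, mean HbA1c: 74.2 ± 9.1 mmol/mol". It does not say whether the cut-off at 63 had already been applied, so both readings are shown for r = 0.9 to 0.5.

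- 74.2 ± 9.1 is the unselected pool: the cut-off is (63 − 74.2)/9.1 = −1.23 SD, and the mean above it is 74.2 + 9.1 × 0.210 = 76.1. The fall is (0.1 to 0.5) × 1.9 = 0.2 to 1.0 mmol/mol.
- 74.2 ± 9.1 is already the selected subset: the implied normal parent is about 53.3 ± 17.8. The fall is (0.1 to 0.5) × 20.9 = 2.1 to 10.5 mmol/mol.

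The documents cannot decide between these. The shared pump effect carries the argument without either.

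**The case against.** The strongest reply is that the trial already has the right test. The sentence before the ANOVA plans a between-arm t-test, the sample size is built on it, and changes shared by both arms do not bias it. Nothing says that GSD-Y will be judged by a within-arm p-value or by comparing significance across arms. Describing the course in each arm is legitimate when the authors expect an early gain that fades, and labelling an analysis as descriptive is often left to a fuller document.

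Most of this stands. A reader might infer that the trial lacks a valid test of GSD-Y, or that its authors intend to claim efficacy from within-arm results; the article supports neither. A reader might also infer that these tests must show improvement whatever GSD-Y does. That is a tendency only: the pump effect has no stated size, it is expected to fade, and with no pump effect the simulated ANOVA is significant in 6 to 25% of trials. Nor can regression to the mean be called large, since one plausible reading makes it at most about 1 mmol/mol. It concerns HbA1c, the selection variable, and does not carry over directly to the questionnaires.

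What does not stand is that the matter is merely left open. The article gives the within-arm ANOVA the same significance level as the t-test and ranks neither. That is a stated choice, not an omitted detail.

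**Conclusion.** The point holds as a fault in a second, unranked inferential analysis, not in the trial's main comparison. A within-arm fall in HbA1c is likely with or without a GSD-Y effect and cannot be attributed to GSD-Y. The illustrative size is 50 to 71% significance in each arm, with the misleading discordance in 21 to 25% of trials. This rests on an assumed shared fall of 3 mmol/mol, SD 9.1, 37 per arm, correlation 0.5 to 0.7 and a paired approximation. Only the SD and the 37 come from the article. Regression to the mean adds an amount that the documents do not fix. The change should be made, but the planned between-arm comparison does not fall with it.

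**What to change.** Replace the within-group ANOVA as an inferential analysis with one longitudinal model of the 6- and 12-month values, containing arm, visit, arm-by-visit, the baseline value and a random effect for start group (the unit that is randomised). State that conclusions about GSD-Y rest on the between-arm contrasts at 6 and 12 months. Report within-arm changes as means with 95% intervals, labelled descriptive and without p-values. Use the same layout for the questionnaires.

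This needs no further patients, visits or measurements. The cost is slightly more analysis work and fewer statements of significance to report. If the model is not wanted, the least change is a sentence making the within-arm results descriptive and resting the conclusion on the between-arm comparison. That removes the misreading but still leaves no between-arm comparison of the course over time.
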